### Data collected from and about Coaches

As noted above, the goal of this experiment is to study and learn from the Coaches as much as the students. The intent is to take what we learn about various approaches to coaching and synthesize it into a Coaching Institute to train future Coaches. To that end, Coaches completed daily evaluations and were debriefed as a group at the end of each day during *Academy* meetings, Research Associates compiled field notes on the approaches used by their Coaches, and individual interviews were conducted with Coaches after the *Academy* meetings and semi-annually between meetings. A sample interview protocol for *Academy* Coaches is included in Additional file 6. Annual student pre-interview surveys and interviews also asked questions about the students’ interactions with and perceptions of their Coach and Coaching Group.

### Quantitative methods and analysis

We collected quantitative data in the forms of yearly pre-interview surveys and yearly evaluations for the *Academy* in-person meetings. Quantitative data will be analyzed using SPSS version 21 [34]. We will utilize a variety of analyses of variances to determine difference between our sample populations of interest (e.g. control vs. experimental, men vs. women, URM vs. non-URM).

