### Student recruitment

On April 10, 2011, an email describing the *Academy* was sent to biomedical graduate school leaders who were members of the GREAT group, graduate directors at other non-medical major research training universities, and leaders of undergraduate diversity STEM programs throughout the U.S. This date was chosen because it was just before the April 15 common deadline for students to make the final decision of where to pursue their PhDs among the offers of acceptance they had received. Those receiving the emails were asked to forward it to incoming PhD students, or undergraduates they had advised who were starting the PhD in fall 2011. It was advertised as multi-year professional development program particularly designed for those with a strong interest in a future academic career. It was made clear from the start that it was a randomized controlled trial of the program; applicants would not be reviewed, ranked or chosen based on credentials or prior experience. Three hundred and fifty students applied for the *Academy*, representing a wide variety of PhD programs in the U.S. From this applicant pool, 100 students were selected to participate in the *Academy*, and 104 students were selected as study controls who received no intervention. The 204 total students recruited for *Academy I* represents the maximum number of students that could be supported under our funding. Eligibility to participate in the *Academy* required: 1) an expressed interest in an academic career in science; 2) U.S. citizenship or permanent residency; and 3) first year PhD student status.

In April, 2012, a similar email was sent to the leaders of biomedical PhD training programs describing the second round of the *Academy II*, but this time asking them to forward it to all PhD students who were within 12–18 months of completing their degrees. Approximately 340 applications were received and were stratified and randomized. For this study, 60 were chosen for *Academy II*, and 61 were chosen for controls (to account for anticipated dropouts of the study) (Figure 1). As we anticipated more drop-offs from beginning PhD students compared to those finishing the PhD, the *Academy II* group is smaller than the *Academy I* group.

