### Analyses

The primary intention of our intervention is to continue supporting interactions between Coaches and their groups, and follow students longitudinally to see if the *Academy* makes a tangible difference in long-term career choices. The hypothesis is that experimental students will have a higher likelihood of pursuing an academic career after the PhD, and that the proportion of URM and non-URM students will be more equal than the past extremely low rate for URM students. These dynamics will be measured through annual interviews with students and quantitative responses on their perceptions of the achievability, desirability, and their commitment to an academic career throughout graduate school and subsequent career steps. These career steps, such as arranging post-doctoral positions that will likely lead to a successful academic career, will provide interim measures.

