Future research will use quantitative and qualitative data to examine longitudinal findings among our experimental and control students. In addition to measuring changes in attitudes regarding the achievability, desirability, confidence, and commitment to an academic career, we will examine students’ endeavors as scientists and the extent to which the social science theories inform and are evident and/or in the background in their everyday experiences. Current funding ensures that students and coaches will be followed for at least three more years, which will put Academy I students past graduation into next career steps, and Academy II students well into one or two next career steps. Further, we will be able to determine if *Academy* coaching and programming impacts the decisions among young life scientists to enter academia, and provided them with the tools needed to succeed.

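### The only method named for the yearly attitude scores is analysis of variance, which makes poor use of students who leave; a mixed model on all surveys would serve better

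*Protocol article*

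**What the plan says.** The Analyses section measures the hypothesis partly through "quantitative responses on their perceptions of the achievability, desirability, and their commitment to an academic career throughout graduate school and subsequent career steps". Quantitative methods and analysis describes the data source and the tool: "We collected quantitative data in the forms of yearly pre-interview surveys", together with evaluations of the in-person meetings, and "Quantitative data will be analyzed using SPSS version 21". The method follows: "We will utilize a variety of analyses of variances to determine difference between our sample populations of interest". The examples of comparisons given there are control against experimental, men against women, and URM against non-URM. No other quantitative method is named.

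The Discussion makes change over time a target ("In addition to measuring changes in attitudes regarding the achievability, desirability, confidence, and commitment to an academic career") and says how long data will keep coming in: "Current funding ensures that students and coaches will be followed for at least three more years".

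Student recruitment shows that losses are expected. It explains the larger size of Academy I with the words "As we anticipated more drop-offs from beginning PhD students compared to those finishing the PhD", and for Academy II says that "61 were chosen for controls (to account for anticipated dropouts of the study". It gives no rate.

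**The concern.** The scores are repeated on the same students over several years, and some students will stop contributing. ANOVA can be applied to such data in two ordinary ways.

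- **One repeated-measures ANOVA.** In its classical form this needs a complete row per student. Anyone with a missing survey is removed, including from the years that he or she answered.
- **A separate ANOVA each year.** Every year uses whoever answered that year. The samples shrink and differ, so a trend across years mixes real change with a change in who is answering.

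Both ignore what a departed student's earlier scores say about the later ones. Precision is lost. There is also a route to bias: waning commitment to an academic career is one of the outcomes and could also be a reason to stop answering. The arms have different reasons to stay in touch, since Academy students have Coaches, groups and meetings and controls receive no intervention. If less committed controls leave more readily, the remaining controls look more committed and the Academy's effect is understated. The reverse pattern would overstate it. Student recruitment says the size of Academy I was capped by funding, so lost students cannot be made up by recruiting more.

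**Working it through.** The article states no power, effect size, dropout rate or number of surveys, so there is no statistical figure to reproduce. The counts agree: 100 + 104 = 204 in Academy I and 60 + 61 = 121 in Academy II.

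**Step 1: share of students lost from a complete-case analysis.** Assume permanent dropout at yearly rate d after the first of w yearly surveys. The complete share is (1 − d)^(w − 1). Both d and w are assumptions; three and six surveys serve as a short and a long case.

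| d per year | complete, w = 3 | lost | complete, w = 6 | lost |
|---|---|---|---|---|
| 3% | 0.97² = 0.941 | 6% | 0.97⁵ = 0.859 | 14% |
| 5% | 0.95² = 0.902 | 10% | 0.95⁵ = 0.774 | 23% |
| 10% | 0.90² = 0.810 | 19% | 0.90⁵ = 0.590 | 41% |

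At 10% and six surveys, Academy I keeps about 59 of 100 Academy students and 61 of 104 controls; Academy II keeps about 35 of 60 and 36 of 61.

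**Step 2: what that does to precision.** Assume a two-sided 5% test and a difference of 0.4 SD, ignoring coaching groups. With everyone analysed, power is 0.82 in Academy I and 0.60 in Academy II. With the completers of the 10%, six-survey case it is 0.59 and 0.39. The full-sample values are a ceiling: a mixed model recovers part of the loss, not all of it.

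**Step 3: when bias arises.** A simulation of Academy I (400 replicates, six surveys, correlation 0.6 between adjacent years decaying with distance) let the arms diverge to a true difference of 0.40 SD at the last survey, an average of 0.20 over all six. The chance of leaving depended on the last observed score, with the log-odds rising by the stated slope per SD of lower score. The rates are those at a score of zero.

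| Dropout | last survey, responders only | six-survey average, complete cases | last survey, all data used | average, all data used |
|---|---|---|---|---|
| 5%, unrelated to score | 0.39 | 0.19 | 0.39 | 0.20 |
| 5%, slope 0.5 in both arms | 0.39 | 0.20 | 0.39 | 0.20 |
| 5%, slope 1, controls only | 0.32 | 0.06 | 0.41 | 0.20 |
| 10%, slope 1, controls only | 0.26 | −0.05 | 0.40 | 0.20 |
| 10%, slope 1 in both arms | 0.38 | 0.17 | 0.40 | 0.19 |

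The last two columns use likelihood-type estimation from every observed survey. When dropout is unrelated to scores, no method is materially biased. When it is related in the same way in both arms, the bias is small. It becomes large when the relation differs by arm. In these runs dropout depends only on observed scores, which is the condition under which the all-data estimator is valid.

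**The case against.** The strongest reply is that the article does not fix what is being criticised. It names a family of methods, not a repeated-measures ANOVA, a yearly ANOVA or a complete-case rule. The sentence lists group comparisons, and the longitudinal aim stands in another section, as future research, without a method. An arm comparison at one time point is a legitimate use of ANOVA. A condensed article may leave the longitudinal model and the missing-data rule to a fuller document, and the named software can fit a mixed model.

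Much of this stands. A reader might infer that the plan will discard withdrawn students, or that its results will be biased. The documents support neither: the form of ANOVA is open, no dropout rate is given, and nothing says that leaving depends on scores or differs by arm. The drop-offs expected in Academy I could mean leaving the PhD rather than ceasing to answer surveys, and the one explicit allowance, in Academy II, is a single extra control.

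A reader might also apply a 3% to 10% miss rate independently to six surveys and report a loss of 1 − 0.97⁶ = 17% to 1 − 0.90⁶ = 47%. That describes intermittent gaps, not withdrawal, and treats six surveys as given.

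What the reply does not remove is that the article does name a method for these survey data and for the arm comparison, and names only one. Under both ordinary forms of it, the earlier surveys of students who left are unused later. That is a point about the stated choice, not only about missing detail.

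**Conclusion.** The concern holds as a choice of method that should be improved, with medium confidence. For yearly attitude scores followed over several years with dropout expected, ANOVA in its usual forms is weaker than a likelihood-based mixed model.

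The certain cost is precision. Under an assumed 3% to 10% permanent dropout per year, a complete-case analysis loses about 6% to 19% of students over three surveys or 14% to 41% over six. Yearly ANOVAs keep more students but on a different, shrinking sample each year. Bias is conditional on dropout that depends on earlier scores, and serious only if that dependence differs by arm; the documents neither state nor exclude this. The point is confined to the attitude scores. Career steps and CVs, which also bear on the hypothesis, are outside it.

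**What to change.** For the yearly attitude scores, replace ANOVA with a linear mixed model that:

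- contains arm, year, arm-by-year and the stratification factors (gender, race and ethnicity);
- allows for correlation between a student's repeated scores, with a random effect for coaching group in the Academy arm only, since controls have no groups;
- is fitted by restricted maximum likelihood to every available survey from every assigned student, including those who later withdrew or left the PhD.

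Take the arm contrast at one survey year fixed before the analysis, separately for Academy I and Academy II. The year must be named, because follow-up is stated only as a minimum. Add a sensitivity analysis that shifts the scores of withdrawn students downwards over a stated range, and report how far the conclusion survives.

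The cost is a change of analysis wording and slightly more analysis work. The mixed-model procedure in the software already named can be used, and no new data are needed. The main model relies on data being missing at random given the observed scores, which is why the sensitivity analysis belongs with it.

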****trial design.**

One of the most critical decisions in designing the *Academy* was whether to include students of all races/ethnicities, or to focus just on URM students. On one hand, it could be argued that an *Academy* for only URM students would concentrate efforts on students who might need these resources most, rather than non-URM students who are more likely to have the resources they need to succeed in the biomedical sciences. However, diversity efforts targeting URM students alone can create a significant stigmatizing effect on those who participate (e.g. [33]). There is also great value in exposing non-URM students to some of the issues and barriers faced by their URM peers as they are discussed in the *Academy* meetings and in the individual coaching groups. Our model also provides opportunities for non-URM students to share inside knowledge that they have gained with their URM peers who may have not yet acquired that knowledge. Finally, the inclusion of both URM and non-URM students was essential in order to determine if the *Academy* differentially could impact URM students vs. all biomedical science PhD students. Therefore, an equal number of men and women were chosen, and equal numbers by race and ethnicity. Thus, for *Academy I*, there are 24 each of Caucasian, Asian, Hispanic and African American students. Only 4 Native American students applied to Academy I, so they were all assigned to the Academy rather than controls as it would not be a meaningful comparison between just 2 students. In *Academy II*, there are 15 each of Hispanic and African American students, 14 each of Asian and Caucasian students, 1 Native American student, and 1 Pacific Islander student. Students in both *Academies* were then assigned to Coaching Groups of 10 students and 1 Coach. These groups were also randomly assigned but stratified such that each group had the maximum diversity possible by gender, race and ethnicity.

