### Activities of coaching and coaching groups between Academy in-person meetings

A core element of the *Academy* trial is the ongoing coaching and relationships between the yearly meetings. The need for and value of a Coach is ongoing, although by no means continuous. The *Academy* experiment is providing a variety of tools and approaches to keeping students and Coaches connected throughout the year. This part of the Academy is also experimental as Coaches and students are provided with several options to use as they prefer. The initial design called for Coaching Groups to have monthly or bi-monthly virtual meetings (video and audio) using a product called Adobe Connect. Over time, some groups have migrated to other virtual meeting platforms, some have stopped meeting formally, and others have adopted alternative ways of keeping in touch. Coaches check in with their students on a regular basis via email or phone as well, and students often contact each other independently. Thus, by not rigidly scripting group behavior, each group has been allowed to organically evolve and we are able to gather data on many different variations. A few webinars around specific topics were also delivered to determine how many individuals would find that mode of information delivery of interests.

The initial funding for the *Academy* trial ran out in August, 2013, but a second grant was obtained from NIH to continue some aspects of the study. The new grant enables support of the Coaches and their groups in their virtual meetings, our delivery of new material and experimenting with other ways to provide content, but does not have sufficient funding to enable the annual meeting. However, based on feedback from the last full meetings in 2013, there was a very strong desire to keep meeting in some way. As a result, we have found alternative funding to enable individual Coaching groups to meet, and a majority of them are making plans to do so in the summer of 2014. The new grant also supports the continuation of logistical support for the Coaching Groups, and full collection of data to study how they function, and the comparison between the *Academy* students and the Control. The Coaches, on their own from day one, made it clear to their students that they would be available to them for as long as they desired irrespective of external funding for the *Academy* study.

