Finally, each of the Coaching Groups was assigned one of our PhD level social scientist Research Associates who observed and took field notes during their meetings. Given that we only had 3 Research Associates and 10 or 6 Coaching Groups, they were unable to be with their groups continuously but rather periodically throughout the meetings.

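### The stated analysis of variance for control vs. experimental has no Coaching Group term, so it understates the standard error of the arm difference if students who share a Coach are positively correlated

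*Protocol article*

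**What the plan says.** Under Student recruitment (the text after Figure 1), the protocol article reports that students in both Academies "were then assigned to Coaching Groups of 10 students and 1 Coach". The groups were formed at random, stratified to make each as diverse as possible. The Data collection section gives the number of groups: "Given that we only had 3 Research Associates and 10 or 6 Coaching Groups".

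The comparison arm has no such structure. Under Student recruitment, for Academy I, "104 students were selected as study controls who received no intervention". For Academy II there were 60 Academy students and "61 were chosen for controls".

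On coaching between meetings, the article explains that "by not rigidly scripting group behavior, each group has been allowed to organically evolve". Some groups changed platform, some stopped formal meetings and others kept in touch in different ways.

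The section Quantitative methods and analysis is brief. It names SPSS and continues: "We will utilize a variety of analyses of variances to determine difference between our sample populations of interest". The examples given are control vs. experimental, men vs. women and URM vs. non-URM. Neither that section nor any other part of the article mentions a group or Coach effect, nesting, a mixed model or an ICC.

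**The concern.** This is a partially nested trial: one arm is clustered and the other is not. Students in a Coaching Group share a Coach and nine peers for two to three years. About half of each in-person meeting is group time, and groups are meant to differ in how they work. Random formation of the groups removes clustering at entry, but not clustering produced by the shared coaching itself.

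An analysis of variance with arm as the factor and students as replicates counts 100 (or 60) independent Academy observations. If group members are positively correlated, there is less information than that. The confidence interval for the arm difference is then too narrow, and the test rejects more often than its nominal level. The contrast affected is the central one: whether Academy students are more likely than controls to move towards an academic career. The error favours declaring a difference that is not there.

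**Working it through.** The article states no power, significance level, effect size or ICC, so there is no figure of its own to reproduce.

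**Inputs from the article**
- Group size m = 10 (Student recruitment).
- Groups: 10 in Academy I and 6 in Academy II (Data collection). Consistency check: 10 × 10 = 100 and 6 × 10 = 60, matching the recruited numbers.
- Academy I: 100 vs 104. Academy II: 60 vs 61 (Student recruitment).
- Controls ungrouped ("study controls who received no intervention").

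**Assumptions, not in the article**
- ICC between 0 and 0.20.
- Two-sided 5% test.
- Equal total variance in the two arms.
- Full follow-up.

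**Formulas**
- Design effect in the Academy arm: DE = 1 + (m − 1) × ICC = 1 + 9 × ICC.
- True variance over reported variance: R = (DE/nT + 1/nC) / (1/nT + 1/nC).
- Standard error ratio: √R.
- Actual alpha: 2 × [1 − Φ(1.96/√R)].

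**Example, Academy I at ICC 0.05**
- DE = 1 + 9 × 0.05 = 1.45.
- R = (1.45/100 + 1/104) / (1/100 + 1/104) = 0.024115/0.019615 = 1.229.
- √R = 1.109, and 1.96/1.109 = 1.77, so alpha = 7.7%.

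| ICC | DE | SE ratio, Academy I | Alpha, Academy I: formula (simulated) | SE ratio, Academy II | Alpha, Academy II: formula (simulated) |
|---|---|---|---|---|---|
| 0 | 1.00 | 1.000 | 5.0% (5.3%) | 1.000 | 5.0% (5.1%) |
| 0.01 | 1.09 | 1.023 | 5.5% (5.4%) | 1.022 | 5.5% (5.7%) |
| 0.02 | 1.18 | 1.045 | 6.1% (6.1%) | 1.044 | 6.1% (6.4%) |
| 0.05 | 1.45 | 1.109 | 7.7% (7.6%) | 1.108 | 7.7% (7.7%) |
| 0.10 | 1.90 | 1.208 | 10.5% (10.3%) | 1.206 | 10.4% (10.2%) |
| 0.20 | 2.80 | 1.385 | 15.7% (16.0%) | 1.381 | 15.6% (15.7%) |

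The simulated values come from 20,000 runs per setting of the two-group analysis of variance (equivalent to a t-test). In the same runs, group means were compared with individual controls using Satterthwaite degrees of freedom. That analysis held type I error between 5.0% and 5.4% at every ICC, in both Academies.

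**Information lost**
- Effective size of the Academy arm is nT/DE. At ICC 0.05 this is 100/1.45 ≈ 69 and 60/1.45 ≈ 41. At ICC 0.10 it is 100/1.90 ≈ 53 and 60/1.90 ≈ 32.
- Difference detectable with 80% power, (1.96 + 0.84) × √(DE/nT + 1/nC), for ICC 0, 0.05 and 0.10: 0.39, 0.44 and 0.47 SD in Academy I; 0.51, 0.56 and 0.61 SD in Academy II. These are large-sample values.

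**The case against.** The strongest reply is that the article does not commit to a student-level model. Its wording is a one-sentence summary with example contrasts, it does not exclude a nested or mixed analysis of variance, and a fuller analysis plan may exist. This stands in part: the text cannot be read as ruling out a group term. However, it names one family of methods for the central contrast, lists only population factors, and nowhere signals that the coached arm has a different error structure. Followed as written, it leads to the wrong standard error whenever the correlation is positive.

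The second reply is that the correlation may be small. Groups were formed at random and balanced on race, ethnicity and gender. Members come from many universities and subfields and keep their own research mentors, and some groups stopped meeting formally. If race or gender predicts the outcome, the balance pushes the unadjusted within-group correlation down. Because groups were random, coaching that changed nothing for anyone would also create no correlation. All of this is fair, and it is why the range starts at zero. Against it, the article expects groups to diverge and treats the differences between Coaches as something to study.

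A reader might infer more than the article supports:
- **That every arm comparison will be wrong.** At ICC 0 there is no inflation, and at 0.01 it is about half a percentage point.
- **That having only 10 or 6 groups further inflates the error of the uncorrected test.** The simulated values match the large-sample formula. Few groups matter for the degrees of freedom of the corrected analysis.
- **That Coaches will be compared statistically with students as replicates.** No such test is planned. Learning about coaching is described through evaluations, debriefs, field notes, interviews and qualitative analysis.
- **That the gender and URM contrasts suffer the same error.** Groups are balanced on these factors, so clustering acts differently there and may work in the opposite direction.

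**Conclusion.** The point holds for control vs. experimental. The design is clustered in one arm only, and the stated analysis makes no allowance for it. The direction is certain for any positive ICC; the size is not, because the article gives no ICC. Under the assumptions listed, the problem is negligible near 0.01 and material from about 0.05, where the true standard error is about 11% larger than the one reported. At 0.10 it is about 21% larger and the actual type I error is roughly double the assumed 5%. The two Academies give almost identical results.

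**What to change.** In Quantitative methods and analysis, replace student-level analysis of variance for control vs. experimental with a partially nested mixed model. It should have:
- a random Coaching Group effect in the Academy arm only;
- each control treated as a singleton;
- small-sample degrees of freedom (Satterthwaite or Kenward-Roger), because there are only 10 and 6 groups.

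An analysis of Coaching Group means against individual controls, with Satterthwaite degrees of freedom, is an acceptable equivalent. For binary career outcomes, state the clustered counterpart. Separate residual variances by arm are optional; with nearly equal arms they change little.

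The change is to wording and model choice only. The study team assigned the groups, so membership is known and no new data are required. The price is somewhat wider confidence intervals, by the standard error ratios tabulated above plus a little for the smaller degrees of freedom. It would also help to report the estimated ICC for each outcome.
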